#### Pain

The level of pain intensity of the participants will be assessed by administering the Numerical Pain Rating Scale (NPRS). The NPRS consists of an 11-point Likert scale, with 0 representing “no pain” and 10 representing “worst imaginable pain". The participants will be asked to indicate the best point that represents the greatest pain they experienced at the time of assessment. Both the Hausa [42] and English [43] versions of the NPRS will be used in the present study. The NPRS has been reported to be a valid, reliable, and responsive measure of pain intensity in patients with LBP [42–44].

#### Functional disability

The levels of functional disability of the participants will be assessed by administering the Roland–Morris Disability Questionnaire (RMDQ). It is a 24-item questionnaire, with scores ranging from 0 (no disability) to 24 (maximum disability). The participants will be asked to tick on any of the 24 items that describe their current disability level. To obtain the RMDQ total score, the items checked are summed up. Both the Hausa [45] and English [46] versions of the RMDQ will be used in the present study. The questionnaire has been reported to be a reliable and valid measure of LBP-related disability [45, 46].

#### Quality of life

The QOL (physical and mental health) of the participants will be assessed by administering the 12-item Short-Form Health Survey (SF-12) questionnaire. The SF-12 is a shorter alternative to the SF-36 Health Survey. The questionnaire measures two health constructs— physical component scores (PCS-12) and mental component scores (MCS-12). A Web-based scoring tool (www.orthotoolkit.com/sf-12/) will be used to calculate the PCS-12 and MCS-12 scores, with higher scores indicating better health status. Both the Hausa [47] and English [48] versions of the SF-12 will be used in the present study. The questionnaire has been reported to be reliable and valid for measuring health-related quality of life [47, 48].

### Interventions

All interventions will be provided twice a week for 8 weeks and under the supervision of the physiotherapists. Participants in the LSE and LSER groups will also carry out the same intervention as for the control group (minimal intervention). All participants will be advised not to partake in any exercise-related interventions during the study. To enhance retention, participants will be contacted by the research coordinator via text messages, WhatsApp messenger, and phone calls on a regular basis to remind them of their treatment appointments  and post-treatment follow-up.

#### Lumbar stabilization exercise (LSE)

Participants allocated to this group will be taught LSE based on the approach of Richardson and colleagues [23] and procedures explained in previous studies [29, 30, 40]. Prior to the training, the participants will be educated with aid of video and pictures on the anatomical location and function of the lumbar spine and the key deep stabilizing muscles with a focus on LMM. They will be asked to assume a prone lying on a treatment table with a pillow placed under the hips to ensure neutral positioning of the spine. Participants will be taught an active isometric contraction of the LMM (with a focus on L2–L5 vertebral level by drawing up the anterior aspect of the pelvic floor or lifting the coccyx to ceiling) in synergy with other deep stabilizing muscles such as TrA (abdominal draw-in maneuver) [30]. Contractions will be held for 10 s and repeated 10 times, with a period of 30- to 60-s rest between repetitions.

#### Lumbar stabilization exercise with real-time ultrasound imaging biofeedback (LSER)

Herein, the intervention will be similar to that described in the LSE group except for the addition of RUSI biofeedback to enhance the precision of contraction and activation performance of the LMM. While maintaining a neutral spine in prone lying, the transducer head of the ultrasound will be placed transversely over the L2–L5 levels and then the participants will be instructed to perform isometric contraction of the LMM and other deep stability muscles as described above. Specifically, they will be instructed to focus on the monitor to see the changes in the thickness of the LMM as they contract the muscles and put in their best effort to increase the thickness with successive contractions. Contractions will be held for 10 s and repeated 10 times, with a period of 30- to 60-s rest between repetitions.

#### Minimal intervention (control)

Participants allocated to this group will receive three exercises as described by van Dieën et al. [49]. These exercises are commonly prescribed for patients with chronic low back disorders. The exercises are knee to chest, lumbar rotation, and bridging. The description and dosage of the exercise are provided in Table 2.

**Table 2 Tab2:** Minimal intervention

	Exercise type	Description	Dosage
1.	Knee to chest	In crook lying position, pull both knees to the chest with interlocked fingers until a comfortable stretch is felt in the hip and lower back. Maintain the highest position	5–10 s hold, 10 reps
2.	Lumbar rotation	In crook lying position, slowly rock knees from side to side as far away as possible and maintain each position	5–10 s hold, 10 reps
3.	Bridging	In crook lying position, lift the pelvis in a straight line as far up as possible and maintain the highest position	5–10 s hold, 10 reps

### Adverse events and safety

Serious adverse events (AEs) are generally rare with therapeutic exercise interventions. All participants will be informed before enrollment about the possibility of experiencing some common AEs associated with exercises such as mild muscle or joint pain and muscle pull, which are often self-limiting. AEs will be recorded during each treatment session as part of the data collection. However, in case of any serious adverse experience (e.g., exacerbating joint pain, marked joint swelling, light-headedness, angina, and shortness of breath or dizziness), it will be promptly reported to the clinical authorities for physician evaluation and further action. Additionally, reports will be sent to the Health Research Ethics Committee of National Orthopedic Hospital, Dala, Kano State, Nigeria. The participants will be allowed or be asked to withdraw from the study if they make such a request or develop serious AEs.

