### Outcome assessment

Primary outcome will be LMM CSA assessed with RUSI whereas secondary outcomes will include pain, functional disability, and QOL to be assessed using self-report questionnaires. All outcomes will be assessed at baseline (−*t*_*1*_), 8 weeks post-intervention (*t*_*2*_), and 3 months follow-up (*t*_*3*_) (Table 1).

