### Sample size calculations

Considering the minimum detectable change of 1.0 cm or 100 mm reported for LMM CSA [50], the sample size was estimated a priori to detect a minimum difference of 1.0 point  in LMM CSA between LSER and LSE, or 2.0 points between LSER and minimal intervention, assuming a common standard deviation (*SD*) of 2.5 points based on our pilot study [29], a medium effect size of 0.32, an alpha of 0.05, statistical power of 85%, and a correlation of 0.5 among repeated measures,  for between–within repeated measures analysis of variance (ANOVA). The calculations revealed that a sample size of 75 is required. However, while anticipating a 20% dropout rate (*n* = 15), a total sample size of 90 (30 per group) will be finally required. The sample size was calculated using G Power 3.1.9.2 software [51].

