## Discussion

Previous small RCT (*n* = 41) suggests that a 4-week LSE training with RUSI biofeedback may improve LMM CSA in patients with non-specific acute LBP compared to analgesics alone [28]. In contrast, in an RCT by Partner and colleagues [31] to compare LMM thickness in patients with NCLBP before and after a single session of LSE with and without biofeedback including the use of RUSI, no significant inter-group difference was detected for LMM thickness. Their study [31] however is underpowered, suffered a small sample size (*n* = 22), and included a single exercise session which may not be adequate to induce a significant change in the outcome observed. Taking into account  methodological limitations of these trials [28, 31], a powered RCT will be conducted to determine  the effectiveness of 8-week LSE training with RUSI biofeedback compared to LSE training without biofeedback, or minimal intervention in individuals with NCLBP. After the intervention, outcomes will be also evaluated at the 3-month follow-up and possibly at the 6-month or 12-month follow-up. If our hypothesis is correct, this study has the potential to inform  the decision to change practice by providing evidence for the clinical effectiveness of LSE with RUSI biofeedback on enhancing recovery of LMM size, which is commonly implicated in LBP and reoccurrence [5]. 

As a secondary objective, the present study will seek to examine the relationship between p ost-treatment change in LMM CSA and pain as well as disability. This may help to establish causality effect regarding LSE training with RUSI biofeedback on LM M morphology (i.e., CSA) and LBP and LBP-related disability.

This study however is without some limitations. The measurement of LMM CSA will be only performed at the L5 level even though aberrations in LMM morphology are commonly observed at this level [30, 41], besides evidence of recovery following specific rehabilitation [28, 30]. Therefore, any changes in the LMM CSA in other levels of the lumbar spine following rehabilitation could not be detected. Furthermore,  other important LMM morphological-related outcomes such as fat infiltration, volume, and percentage thickness will not be evaluated due to limited resources. Nevertheless, the planned powered, single (assessor) blind, three-arm (including comparator and active control groups), parallel RCT design is the strength of our study.  

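### Routine adverse event recording is tied to treatment sessions, so non-serious events after a participant stops attending, or after week 8, have no stated route of capture

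*Protocol article*

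**What the plan says.** The section on adverse events and safety gives one routine rule: "AEs will be recorded during each treatment session as part of the data collection". For serious adverse experiences it adds that "it will be promptly reported to the clinical authorities for physician evaluation and further action", with reports also going to the ethics committee. On leaving the study it says: "The participants will be allowed or be asked to withdraw from the study if they make such a request or develop serious AEs".

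The Interventions section fixes when sessions occur: "All interventions will be provided twice a week for 8 weeks and under the supervision of the physiotherapists". It also says that "participants will be contacted by the research coordinator via text messages, WhatsApp messenger, and phone calls on a regular basis". The purpose given for these contacts is to remind people of treatment appointments and post-treatment follow-up; asking about AEs is not mentioned.

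Under Outcome assessment, "All outcomes will be assessed at baseline", at 8 weeks and at 3 months. The Discussion places the later visit after treatment: "After the intervention, outcomes will be also evaluated at the 3-month follow-up and possibly at the 6-month or 12-month follow-up". AEs are not among the listed outcomes, and the statistical analysis section describes no comparison of AEs between groups. The sample size section sets the total of 90 "while anticipating a 20% dropout rate".

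**The concern.** Tying AE recording to attendance makes the record depend on something that an AE can itself bring to an end. The events the protocol expects are minor muscle or joint soreness and strains. These could plausibly make someone with back pain stop coming, and a person who stops has no later session at which to be asked. After week 8 nobody has a session.

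The arms also differ in what they do. Both stabilization arms perform the control exercises plus ten contractions held for 10 seconds. Stopping because of an event could therefore differ between these arms and control, and the recorded counts alone would not show it.

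What is at stake is the by-arm description of harm that a reader would expect in the trial report, and any statement that the exercise programmes were well tolerated.

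**Working it through.** The protocol gives no AE rate, AE sample size or AE analysis, so there is no planned AE figure to reproduce. The check covers the timeline, the number of people affected, and what incomplete recording does to a by-arm description.

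**1. Where AEs could be picked up**

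- Treatment sessions, weeks 1 to 8: routine AE recording stated.
- 8-week and 3-month assessments: outcomes stated, AE enquiry not stated.
- Reminder calls and messages: stated, but as reminders.
- Participants who stop attending: no AE enquiry stated.
- Serious adverse experiences: prompt reporting stated, not limited to sessions. This says what happens once an event is known; it sets no occasion for finding out.

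The gap is therefore non-serious events that arise after the last attended session.

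**2. Share of the observation period with routine recording**

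Treatment lasts 8 weeks = 56 days. Take 3 months as 91.3 days, about 13 weeks.

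- Counted from the end of treatment, as the Discussion suggests: 56 / (56 + 91.3) = 0.38, about 8 of 21 weeks. About 13 of 21 weeks (62%) have none.
- Counted from baseline: 56 / 91.3 = 0.61, about 8 of 13 weeks. About 5 of 13 weeks (38%) have none.

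These are shares of calendar time for someone who attends to the end, not shares of events. Exercise-related events may well cluster in the treatment weeks.

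**3. How many people could stop early**

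The protocol's own dropout count is 15, which is 20% of 75 (0.20 × 75 = 15; 75 + 15 = 90). Applied to the 90 randomized, 20% is 0.20 × 90 = 18. Both are upper bounds for this purpose, because dropout is not split by timing: a person missing only the 3-month visit may have complete session records.

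**4. Effect on a count (assumed figures)**

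Suppose 6 of 30 in one arm have a pain flare, and 3 of them stop because of it before anyone records it. The recorded rate is 3/30 = 10% instead of 6/30 = 20%.

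**5. Effect on a by-arm contrast (assumed figures)**

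Let the true risks be p1 and p0, and the fractions recorded s1 and s0. The recorded risk difference is p1·s1 − p0·s0 and the recorded risk ratio is (p1·s1)/(p0·s0).

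| p1, p0 | s1, s0 | Difference | Ratio |
|---|---|---|---|
| 0.30, 0.20 | 1, 1 | 0.10 | 1.50 |
| 0.30, 0.20 | 0.8, 0.8 | 0.24 − 0.16 = 0.08 | 1.50 |
| 0.30, 0.20 | 0.8, 0.9 | 0.24 − 0.18 = 0.06 | 1.33 |
| 0.30, 0.20 | 0.9, 0.8 | 0.27 − 0.16 = 0.11 | 1.69 |
| 0.20, 0.20 | 0.8, 0.9 | 0.16 − 0.18 = −0.02 | 0.89 |
| 0.20, 0.20 | 0.9, 0.8 | 0.18 − 0.16 = +0.02 | 1.13 |

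Counts fall in every row with incomplete recording. Equal loss shrinks the difference and leaves the ratio alone. Unequal loss can move either measure up or down.

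**The case against.** The strongest reply is that the sentence on recording is not wrong. It does not say that AEs are recorded at sessions and nowhere else, and this is a journal article condensing a fuller protocol that may well cover follow-up visits and non-attenders. That lowers confidence in what will actually be done. It does not remove the point: the article does state when AEs are recorded, and that rule, followed as written, makes capture depend on attendance.

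A reader might infer something stronger: that all events during follow-up are missed and that the comparison of harm is biased toward finding none. The document does not support this, for four reasons.

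- Serious adverse experiences have their own route, not limited to sessions, and its examples include worsening joint pain. Events at a supervised session the participant attends are covered too.
- Pain and disability are measured at 8 weeks and 3 months, so lasting deterioration in those assessed would be visible there.
- No between-arm AE comparison is planned, so there is no specified test to be biased.
- All arms share the same session schedule and dropout is not given by arm, so the direction of any distortion is unknown. The argument from extra exercise load also does not separate the two stabilization arms, which do similar exercises apart from the imaging feedback. The instruction to give best effort appears only for the feedback arm.

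It is also fair to say that the calendar shares overstate the gap if most events occur during treatment weeks.

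**Conclusion.** The point holds in a limited form. Non-serious events after the last attended session, and after week 8 for everyone, have no stated route of capture. Routine recording covers about 38% of the period to the 3-month visit if that visit is timed from the end of treatment, and about 61% if timed from baseline. AE counts per randomized participant would be understated to the extent that such events occur; the document gives no rate from which to say by how much. A by-arm description could be distorted in either direction if stopping because of events differs by arm.

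This rests on the recording rule being applied as written and on no wider rule standing in a document not shown. It does not touch the primary analysis. It is a weakness in safety data that is cheap to correct.

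**What to change.** Record AEs in every randomized participant from randomization to the 3-month visit, whether or not they still attend:

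- Ask one fixed AE question at each session, at the 8-week and 3-month visits, and in the reminder calls and messages already planned.
- When someone misses sessions or stops, use that contact to record the reason and whether an event caused it.
- Have the research coordinator or treating staff ask, so that the radiologist and the questionnaire assessor stay blinded.
- Report AEs, and stops due to AEs, per randomized participant by arm.

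The cost is one question at contacts that already take place and a line or two in the safety section. Recorded AE counts will be higher, which is the purpose.

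Timing matters. The Trial status section expected follow-up to be complete by September 30, 2021, before the article was published. If data collection has ended, prospective capture is possible only in any 6- or 12-month follow-up that goes ahead. In that case the report should state the window in which AEs were recorded, give AEs and known stops due to AEs by arm, name this limitation, and make no tolerability claim beyond the treatment sessions.

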### Data processing and statistical analyses

All data will be carefully recorded in a logbook and electronically using Microsoft Excel sheets. Data values will be double-checked for missing values and errors before transfer into SPSS for reporting and statistical analysis. Intention to treat (ITT) analysis will be applied with all randomized participants who have any outcome data available for analysis, included in the trial regardless of the presence or absence of follow-up. All statistical analyses will be conducted on IBM SPSS Statistics version 23.0 (IBM Co., Armonk, NY, USA) with a *P*-value < 0.05 to be considered significant for all tests.

A normality test for the dependent variables will be examined using the Kol mogorov–Smirnov and Shapiro–Wilk test. Descriptive analysis will be used to summarize the data with the use of mean (SD), frequencies, and percentages. One-way ANOVA (for normally distributed data) or Kruskal–Wallis (for skewed data) test will be used to compare baseline continuous variables whereas the chi-square test will be used to compare baseline categorical variables among the three groups. Mixed between–within subject ANOVA will be applied to evaluate time effect, group effect, and group by time interaction effect  in all outcomes if the data is normally distributed. Otherwise, Friedman’s ANOVA and Kruskal–Wallis test will be applied to evaluate within-group and between-group differences, respectively, when the data is skewed. Post hoc analysis will be applied for any significant within- or between-group differences detected. The effect size will be computed to evaluate the magnitude of change in all the outcomes. To examine the relationship between changes in LMM CSA and pain or disability, correlation and regression analyses will be performed for all the intervention groups.

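### The serious-adverse-event rule asks participants to leave the study rather than only the exercises, so their later outcomes are lost to the planned ITT comparison; the resulting bias is probably small and cheap to avoid

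*Protocol article*

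**What the plan says.** Three statements in the protocol article bear on this point.

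- **Withdrawal rule** (Adverse events and safety): "The participants will be allowed or be asked to withdraw from the study if they make such a request or develop serious AEs". What is left is the study, and the participant may be asked to leave as well as allowed to. Nothing in the article says that outcomes are still collected afterwards.
- **Trigger** (same section): the examples of a serious experience include "exacerbating joint pain, marked joint swelling, light-headedness", followed by angina, breathlessness and dizziness. The section opens with "Serious adverse events (AEs) are generally rare with therapeutic exercise interventions" and gives no rate.
- **Analysis** (Data processing and statistical analyses): "Intention to treat (ITT) analysis will be applied with all randomized participants who have any outcome data available for analysis". By the same sentence, these participants count whether or not they were followed up. The main method is stated as "Mixed between–within subject ANOVA will be applied to evaluate time effect, group effect, and group by time interaction"; rank-based tests replace it if the data are skewed.

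Under Outcome assessment, every outcome is measured at baseline, 8 weeks and 3 months.

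**The concern.** An ITT comparison needs outcomes from everyone randomized, including those who stop treatment. A rule that ends study participation after a serious adverse event removes those outcomes by design. The removal is not obviously unrelated to what is measured: worsening joint pain is one of the listed triggers, and pain and disability are secondary outcomes. If the people removed would have scored worse than those who remain, their arm looks better than it was. If this happens unequally across arms, the treatment comparison is distorted. The dropout allowance in the sample size replaces lost numbers but does not correct selective loss.

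**Working it through.** **1. Following the rule through the analysis.** Adverse events are recorded at treatment sessions, and treatment lasts 8 weeks, so a withdrawal under this rule would usually come before the first post-treatment assessment. The participant then has a baseline value only. Baseline counts as outcome data, so the ITT sentence keeps the person in the set. A between–within ANOVA as usually run uses only participants with all three measurements, so this person contributes nothing to the group-by-time test. Here mixed means between- and within-subject factors; it is not a likelihood-based mixed model. Even such a model would assume that the missingness is explained by observed data, which is doubtful for someone removed after worsening since the last assessment. The rank-based fallback does not help either: Friedman's test needs all time points, and a Kruskal–Wallis test at follow-up needs the follow-up value.

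**2. The plan's own figure.** The point does not rest on the sample size, but that figure reproduces. For the between-groups effect in a repeated-measures ANOVA with 3 groups, 3 measurements (m), f = 0.32 and correlation ρ = 0.5:

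λ = N·f²·m / (1 + (m − 1)·ρ) = 75 × 0.1024 × 3 / (1 + 2 × 0.5) = 11.52

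With 2 and 72 degrees of freedom and alpha 0.05, power is 0.854 against the stated 85%. Adding 15 for dropout gives 90, or 30 per arm. That allowance covers loss from all causes.

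**3. Shift in one arm's mean.** Let k of 30 be lost, with outcomes that would have been g points worse than the mean m₀ of those remaining. Taking worse as higher, as on the NPRS:

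full-arm mean = [(30 − k)·m₀ + k·(m₀ + g)] / 30 = m₀ + (k/30)·g

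The observed mean is m₀, so the arm looks better by (k/30)·g.

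The documents give neither k nor g. Assume k = 1 to 3 and g = 3 points on the 0–10 NPRS:

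| k | (k/30) × 3 |
|---|---|
| 1 | 0.1 |
| 2 | 0.2 |
| 3 | 0.3 |

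The shift is proportional to g. With g = 1 the same range of k gives 1/30 = 0.03 to 3/30 = 0.1.

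**4. Bias in a comparison of two arms.** This is the difference of the two shifts, (k₁g₁ − k₂g₂)/30. With g = 3 in both arms:

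- 2 lost in each arm: 0.2 − 0.2 = 0
- 3 against 1: 0.3 − 0.1 = 0.2
- 3 against 0: 0.3

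**5. The same formula for cross-sectional area.** The sample size section gives an SD of 2.5 points and a target of 1.0 point between the biofeedback and plain exercise arms. Assume those lost would have been 0.5 to 1.5 SD worse:

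- smallest case: 1/30 × 0.5 × 2.5 = 0.04 points
- largest case: 3/30 × 1.5 × 2.5 = 0.375 points

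These figures show only what would follow if such a gap existed. Nothing in the protocol establishes one for this outcome.

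**The case against.** The strongest reply is that this is a wording matter of little consequence. The sentence runs a participant's own request together with serious events, does not make removal compulsory, and does not expressly say that assessments stop. The protocol calls serious events rare and describes mild muscle or joint pain as a separate, common and self-limiting class, so ordinary flares are not the trigger. Light-headedness or angina has no shown link to later back pain. A condensed article may also leave follow-up after discontinuation to the full protocol.

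Much of this stands, and it limits the size of the problem. It does not remove it: the article states a rule, the rule concerns the study rather than the exercises, and its natural consequence is that later visits do not happen. Withdrawal at the participant's own request is legitimate and is not at issue.

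A reader might infer more than the documents support:

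- **That these participants are formally excluded after randomization.** The ITT sentence keeps anyone with outcome data, whether or not they were followed up. What is lost is the later values.
- **That the full 20% dropout, 6 of 30 in an arm, could be driven by serious events.** The allowance is for all causes, and the protocol calls serious events rare.
- **That the active arms are favoured.** Both exercise arms also perform the control exercises, and the treating physiotherapists know the allocation, so unequal withdrawal is conceivable. No difference in event rates is documented, and the two exercise arms differ only in the ultrasound biofeedback.
- **That the primary outcome is biased.** The link runs most directly to pain and disability. For cross-sectional area it is plausible but not shown.

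**Conclusion.** The concern holds as a limited one. The withdrawal rule and the ITT commitment do not fit together: followed as written, participants asked to leave after a serious event stay in the analysis set in name but drop out of the group-by-time comparison, for a reason that can relate to pain and disability. The likely size is small, about 0.1 to 0.3 NPRS points in one arm's mean. That range assumes 1 to 3 of 30 withdrawn and a 3-point gap, neither of which the protocol supplies. It becomes bias in the treatment comparison only if withdrawals or gaps differ between arms. The change is worth making because it costs little and removes an avoidable source of missing data.

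**What to change.** Reconcile Adverse events and safety with Data processing and statistical analyses. State that a participant who stops the trial exercises because of an adverse event is still invited to all remaining outcome assessments and is analysed in the allocated arm, unless consent to follow-up is withdrawn. Leave the clinical decision on stopping exercise as it is.

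Timing limits what can still be collected. The Trial status section expected follow-up to end by 30 September 2021, and the current version was approved on 4 October 2021. Where the 8-week and 3-month visits have already passed, report withdrawals for adverse events by arm and add a sensitivity analysis for their missing outcomes, for example one that assumes values worse by a range of amounts in each arm. The new sentence would still apply to the 6- or 12-month follow-up that the Discussion mentions as possible.

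The cost is about one sentence, one sensitivity analysis, and a few follow-up visits from participants no longer on treatment, using the reminder contacts already planned under Interventions.
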